#### **6.5 Laboratory investigations**

Parasite count will be performed once every morning during admission, repeated on days 7, 14 and 28, and on any other day(s) of complaints. Counts will be made against 200 white blood cells (WBC) on a thick blood smear and quantified per  $\mu\text{L}$  using the baseline WBC count of 8,000 and multiplying each by 40.

Blood for haematology and clinical chemistry, together with urine for routine urinalyses will be obtained on admission, on the last day of study drugs (day 3) and at day 7. Further testing will not be performed unless clinically indicated.

Haematological tests will include: haemoglobin, and where appropriate total and differential white blood cell count and platelet count

Biochemical parameters will include creatinine, total bilirubin, alanine aminotransferase (ALT) and albumin.

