### **4. TRIAL DESIGN**

#### **4.1 Primary end point**

The primary end-point of the trial will be treatment failure by day 28. This will be defined as:-

*Any of:-*

- 1) a need for rescue treatment due to clinical deterioration defined by altered sensorium, convulsions, persistent vomiting, renal impairment, respiratory distress, a fall in Hb below 7g/dl, or in cases where initial haemoglobin was less than 9 g/dl a drop of 20% from the starting Hb, at any time during admission;
- 2) persistence of fever with parasitaemia on day 3;
- 3) increasing parasite load on day 3;
- 4) failure to clear parasites on day 7;
- 5) rescue medication for recurrent malaria before day 28;
- 6) slide parasite positivity at day 28.

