## **4.2 Secondary endpoints**

Secondary endpoints will include the following:-

1. Incidence of foetal death during treatment, defined as absence of foetal heartbeat assessed by Doppler;
2. Hypoglycaemia requiring treatment;
3. Parasite recrudescence or re-infection on day 14;
4. Parasite clearance on day 3;
5. Level of recovery of haemoglobin on day 14;
6. Fever clearance time;
7. Incidence of perinatal and neonatal mortality, assessed 4-6 weeks after due date of delivery;
8. Clinically apparent neonatal abnormality, assessed 4-6 weeks after due date of delivery;
9. Placental malaria
10. Preterm delivery
11. Other adverse events during treatment.

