### **6.6 Follow up to day 28.**

On discharge from the ward, patients will be requested to attend follow up clinics at the hospital on days 7, 14, 21 and 28 and at any time they have a clinical problem before day 28. Village Health Workers will visit them daily at home up between discharge and day 7, and if they do not attend follow up. During clinic visits the progress will be reviewed, complaints recorded, and laboratory specimens (blood smear, 2-3 mls blood for full blood picture, drug assays etc) collected when appropriate. Temperature and pulse will be measured and recorded. At the end of each clinic, members of the study team will follow all “no show up cases” to their homes to record reasons for not showing up, explain the importance of adhering to stipulated follow up days and to collect clinical and laboratory variables. During daily home visits VHWs will elicit any history of drug intake outside the study team and record progress using a simple standardised questionnaire, collect blood smears from febrile women and submit it to the study team for microscopy. The VHW will refer sick women to the study team for review and expert management.

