The PI will maintain a) a drug receipt form to confirm that supplies have been received b) a list of all drugs given to and returned by the dispensing nurse and c) a record of all unused drugs. Study drugs will only be used according to the study protocol; any discrepancy should be explained.

All personal demographic identification and clinical data/history will be recorded in the medical records to constitute the Source document (SD). The clinical data and laboratory results will be transcribed in the Clinical Report Form (CRF). The SDs and CRFs will be kept separately at the office of the PI.

The day of first treatment is day 0. Day 14-cure rate is the primary end point of therapeutic efficacy. It is the proportion of treated patients with no asexual parasitaemia on day 14, and who did not receive rescue medication.

An efficient medication should increase the haemoglobin level by at least 1 g/dl within 14-28 days of starting treatment, assuming no other causes for blood loss. To avoid group differences in taking iron/folate supplements, the study team will ensure that all participants receive standard routine care.

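### Day-14 haemoglobin is an endpoint with no routine measurement behind it, and day 3, which the primary endpoint uses, is numbered in two ways

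*Protocol*

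**What the plan says.** **Endpoints.** Protocol section 4.1 includes among the six failure criteria "persistence of fever with parasitaemia on day 3" (item 2) and "increasing parasite load on day 3" (item 3). Item 1 includes a haemoglobin trigger that applies while the woman is an inpatient. Section 4.2 lists "Parasite clearance on day 3" (endpoint 4) and "Level of recovery of haemoglobin on day 14" (endpoint 5). Section 11 repeats both as pre-planned analyses.

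**Laboratory schedule.** Section 6.5 takes blood for haematology on admission, "on the last day of study drugs (day 3) and at day 7", and continues: "Further testing will not be performed unless clinically indicated". Parasites are counted each morning of the admission, again on days 7, 14 and 28, and on any day with complaints.

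**Visits.** Section 6.3 admits every woman for three days. Section 6.6 sets clinic visits on days 7, 14, 21 and 28, where a full blood picture is optional. Village health workers visit daily from discharge to day 7 and "collect blood smears from febrile women".

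**Day numbering.** Appendix 2 states: "The day of first treatment is day 0". Appendix 1 gives study drug on days 0, 1 and 2, and its next column is day 7. Its haematology row is ticked on days 0 and 7 only.

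**The concern.** An endpoint can be analysed only if the schedule produces the measurement.

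If day-14 haemoglobin is taken only where a clinician sees a reason, the values come from women who differ from the rest. That selection may also differ by arm: section 4.3 states blinding for the slide reader only, so the decision to test could follow knowledge of the treatment. Values that were never measured cannot be recovered in analysis.

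For day 3 the stake is classification. Parasite clearance and parasite trend at 48 hours and at 72 hours are different quantities. If the protocol permits both readings, two analysts could classify the same woman differently on the primary endpoint. Afebrile women are a planned part of this population, because section 5.2 admits asymptomatic women with at least 1000 parasites/µL. A smear rule triggered by fever would miss them.

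**Working it through.** The check sets the days each endpoint needs against the days the protocol schedules.

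**Step 1: day-14 haemoglobin.**

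| Source | Routine haematology days | Day 14 included? |
|---|---|---|
| Section 6.5 | admission, 3, 7 | No, and later tests only on indication |
| Appendix 1 | 0, 7 | No |
| Section 6.6 | none fixed; optional at clinic visits | Not routinely |

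Shifting the day labels by one does not bring day 14 into any row, so the gap exists under either numbering. Appendix 2 expects a haemoglobin rise of at least 1 g/dl over days 14 to 28, yet no routine value is scheduled after day 7.

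Size: the October 2004 revision gives 72 per arm. For 1% versus 15%, two-sided 5% and 80% power, the usual formula gives 58 without and 72 with a continuity correction, so that figure is reproduced. Four arms give 4 × 72 = 288 women, with 0 scheduled day-14 haemoglobins.

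**Step 2: which day is day 3?** Each three-day regimen is given on three consecutive days, so last dosing day = first dosing day + 2.

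- Appendices 1 and 2: first dose on day 0, so the last dose is on 0 + 2 = day 2. Day 3 is 3 × 24 = about 72 hours after the first dose.
- Section 6.5: last dose on day 3, which implies a first dose on 3 − 2 = day 1. Day 3 is then (3 − 1) × 24 = about 48 hours after the first dose.

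**Step 3: what is available on day 3 under each reading?**

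| | First dose = day 1 (section 6.5) | First dose = day 0 (Appendices 1 and 2) |
|---|---|---|
| Place | third inpatient day | may fall after the three-day admission |
| Smear | every woman | febrile or symptomatic women, and any still admitted |
| Item 2 (fever with parasites) | scorable | largely covered, since it needs a smear only if fever is present |
| Item 3 (rising load) | scorable | no scheduled smear in discharged afebrile women |
| Secondary endpoint 4 (clearance) | scorable | no scheduled smear in discharged afebrile women |

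**Step 4: inpatient haemoglobin for item 1.** Section 6.5 orders haematology on the last dosing day, which lies within the admission. Appendix 1 shows none between day 0 and day 7. A team working from the table would not take a value that the text requires.

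**The case against.** A reader might infer that there is no day-3 assessment at all and that the day-3 components of the primary endpoint cannot be scored. The document does not support that. Section 6.5 names a day 3, has parasites counted every morning of the admission, and section 6.3 has temperature taken throughout treatment. In that numbering every woman has the data. Under day-0 numbering, item 2 is still largely covered. Only febrile women need a smear for it, home visits are daily, and Appendix 1 asks for a smear at any complaint of fever. It also keeps temperature monitoring going until a woman has been afebrile for 24 hours. Section 6.3 allows for stays beyond the treatment days, though it does not guarantee them.

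A reader might also infer that item 1 lacks an inpatient haemoglobin. It does not: section 6.5 orders one. What remains is that the schedule table omits it.

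A further argument is that a rising parasite count missed on day 3 would probably be caught by the day-7 clearance criterion (item 4). That limits the effect on the composite. It does not help secondary endpoint 4, and it does not settle which hour item 3 refers to.

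For day-14 haemoglobin, one can say that measurement was evidently intended: the endpoint names the day, day 14 is a clinic visit, and a blood picture may be taken there. The intention is clear, but no passage makes the test routine, and the limit in section 6.5 works against it. A statistical analysis plan could define windows or missing-data rules, but it could not supply values that were not collected.

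**Conclusion.** The point holds in three parts.

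1. Day-14 haemoglobin is a declared endpoint and a pre-planned analysis with no routine measurement under any day numbering. One of eleven secondary endpoints is affected. That the resulting subset would be selected follows from the testing rule. That the selection would differ by arm is a possibility, not something the protocol shows.
2. Day 3 carries two meanings, about 48 or about 72 hours after the first dose. This makes two of six primary items (2 and 3) and secondary endpoint 4 ambiguous. The loss of data is narrower: under day-0 numbering it falls mainly on item 3 and secondary endpoint 4, in afebrile women already discharged. Its size cannot be calculated, because the protocol gives neither the proportion afebrile nor the actual day of discharge.
3. Section 6.5 and Appendix 1 conflict on the inpatient haemoglobin that item 1 uses. This is an inconsistency between text and table, not proof of a missing measurement.

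The ambiguity lies inside the primary endpoint and the missing values cannot be obtained later, so the passages should be reconciled before further women are enrolled.

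**What to change.** - Adopt one day numbering throughout, state how many hours after the first dose day 3 falls, and reconcile section 6.5 with Appendices 1 and 2. Which reading was meant is for the investigators to say.
- Add a day-3 column to Appendix 1 with a smear and a temperature for every woman, whether still admitted or at home.
- Carry the day-3 haemoglobin already ordered in section 6.5 into Appendix 1.
- Add haemoglobin for every woman at the existing day-14 visit, from the finger-prick already taken for the smear, and exempt it from the section 6.5 limit on later testing.

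Cost: an edit to section 6.5 and the schedule table, and one extra haemoglobin reading per woman. If day 3 falls after discharge, there is also one extra smear per woman at the daily home visit already planned. The day-3 haemoglobin adds nothing, since section 6.5 already orders it.

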### *HIV testing.*

There is a possibility that HIV co-infection could significantly alter the efficacy of antimalarial drugs in pregnant women- certainly this seems to be the case for SP [Kisumu]. It may also affect birth outcome. It is hoped that in a randomised design the number with HIV will be balanced between the groups, which based on the blood donor seroprevalence is unlikely to be a large number in any group. Knowing the HIV serostatus of women enrolled would however be ideal, as at a minimum it would allow for stratification by HIV status (negative, positive or not known).

The Ministry of Health in Tanzania has recently recommended that all pregnant women should be offered HIV testing after pre-test counselling. In Teule hospital nevirapine is currently available for HIV positive women around the time of delivery. Major efforts are being made in Teule hospital to provide structured support for those found HIV positive, and home-based palliative care for those with advanced HIV disease. The study team will follow national and hospital guidelines for women enrolled in the study, and offer testing after pre-test counselling to all women, as for any other pregnant women as part of routine antenatal care. Where they agree to testing the results will be recorded if they consent to this. Agreeing to HIV testing will not, however, be a pre-condition of entry to the trial. The study team considers that anonymous testing would be unethical in the context of this study. Currently take-up of HIV testing is low in Muheza district despite a very positive attitude to it from Teule senior staff and those who accept HIV testing may well be systematically different in terms of HIV risk from those who refuse. This study is therefore unlikely to be the ideal platform to examine the interactions between HIV and antimalarial drugs in pregnancy.

### **6.6 Follow up to day 28.**

On discharge from the ward, patients will be requested to attend follow up clinics at the hospital on days 7, 14, 21 and 28 and at any time they have a clinical problem before day 28. Village Health Workers will visit them daily at home up between discharge and day 7, and if they do not attend follow up. During clinic visits the progress will be reviewed, complaints recorded, and laboratory specimens (blood smear, 2-3 mls blood for full blood picture, drug assays etc) collected when appropriate. Temperature and pulse will be measured and recorded. At the end of each clinic, members of the study team will follow all “no show up cases” to their homes to record reasons for not showing up, explain the importance of adhering to stipulated follow up days and to collect clinical and laboratory variables. During daily home visits VHWs will elicit any history of drug intake outside the study team and record progress using a simple standardised questionnaire, collect blood smears from febrile women and submit it to the study team for microscopy. The VHW will refer sick women to the study team for review and expert management.

### **7 Follow up at birth and after delivery.**

- (a) Birth outcome will be recorded for all study mothers who deliver in Teule hospital (currently between 70 and 80% of those who attend antenatal clinics). This will include maternal mortality, perinatal mortality, maternal complications, and whether the new-born baby has any clinically apparent abnormalities.

- (b) Patients will be followed up at home by VHWs on day 7 after birth for kernicterus. Previous studies have demonstrated that following up at home works well in Muheza district.
- (c) Patients will be encouraged to bring their babies to Teule for routine immunisation one month after birth, and assessed for birth outcome at that point. At 6 weeks after due date, all mothers (whether giving birth in Teule or not) who have not attended will be followed up at home. Assessment at that time will include birth outcome, or a serious problem since birth such as kernicterus, and the baby will be examined for congenital abnormalities. In the case of a neonatal or maternal death a history will be taken from the main carer or any healthcare workers involved to try and ascertain the cause of death. Whenever the mother has moved from the area all possible efforts will be made to ascertain birth outcome.

## 7 Sample size and duration of study.

**NOTE ADDED Oct 2004- the sample size calculation in italics is the original one. There is a revision following slow recruitment due to local control measures. This is in normal font and blue.**

*Sample size has been calculated based on treatment failure as defined in section 4.1. If the response of pregnant women to antimalarial treatment is similar to that of children in Muheza, the proportion of women with treatment failure by day 28 in the SP+Placebo group will be at least 45%, the parasitological clearance failure rate among sick children at the study site ([name] et al., 2001). A Cochrane data review of studies of amodiaquine in Africa showed a day 14 clearance failure rate on amodiaquine alone was 17% (Olliaro and Mussano, 2000) leading to a theoretical failure rate for SP+Amodiaquine of at least 8% ( $0.45 \times 0.17$ ) if there is no interaction between these drugs. In the Gambia, day 14 failure rate with SP+Artesunate was 1.6% (von Seidlein et al 2000). Assuming the 28-day failure rate of 4% with artesunate alone, the failure on amodiaquine+artesunate is estimated at at least 1% ( $0.17 \times 0.04$ ). In this study, it is assumed that the best treatment would achieve 5% failure rate. We will consider anything up to 10% failure rate to be equivalent for public health purposes.*

*Allowing for a 10% defaulter rate approximately 40 women per group would be sufficient to detect a five fold decrease in the risk of treatment failure in the three combination groups compared to the SP group. However this sample size is insufficient for comparing the risk of treatment failure between the different combinations. It is important to compare the efficacy of SP+ amodiaquine versus the combination including artesunate as the latter combination is likely to be more expensive and hence advantage over the former needs to be defined. Thus, in order to detect a 4 fold difference in treatment failure between SP+Amodiaquine and amodiaquine+artesunate group (eg 8% vs 2%) with 95% precision and 80% power, we will enrol 80 women in the SP+placebo group and 240 women in each of the other three groups.*

*Based on the sample size of 80 women on SP alone and 240 in each of 3 combination regimens while allowing for 10% loss to follow up, a total of 900 women will be enrolled in the study. According to records at MCH for year 2000, a total of 6,880 pregnant women (approximately 20 per day) attended the antenatal clinic, of which an average of 6 per day had complaints. We assume that 3 of the sick 6 will have falciparum malaria and that 2 of them will consent to participate. Therefore, it will take 450 working days to enrol 900 women and the duration of the study is estimated to be 2 years.*

*The sample size should be adequate and sufficiently robust to detect common side effects in pregnancy. Rare side effects can only be detected in large Phase 4 and post-marketing surveillance studies. This study should provide information which can allow such studies to be undertaken.*

**Oct 2004.** Vigorous measures to protect pregnant women in the district from malaria on a general background of reduced transmission of malaria in this area have fortunately led to substantial reductions in the number attending the antenatal clinic with clinical malaria. The investigators reviewed the data from other sites, and it is clear there is still likely to be a critical shortage of data on antimalarials in pregnancy from Africa, so a trial even with an ability to detect this relatively large difference is likely to be of considerable utility to policymakers. A revised sample size has been calculated to detect a difference at day 28 from 1% (the best likely failure rate in any arm) and 15% (above which no drug could be deployed). This gives a sample size of 72 in each arm when  $\alpha$  was .05 and  $\beta$  0.8. This would be capable of detecting common, but not rare, adverse events. The trial will continue on this basis due to the public health importance of this question.

## **9 Stopping rules/discontinuation criteria (finalised after meeting of the DSMB)**

*Parasite clearance:* The study has to balance the Tanzania government's recent policy to use SP as first line drug treatment against a high SP-resistance in Muheza district. We assume that around 45% of women in the SP group will need escape medication. Since all women will be admitted to the study ward, the escape medication will be administered on time and complications arising from the use of a relatively ineffective drug should be minimal. However, if the proportion of women needing escape medication is  $\geq 40\%$  in any arm of the study, we will discontinue that arm when 50 women are enrolled which will give a confidence limit of 25-55% for the estimated treatment failure rate.

*Side effects.* All serious possible side-effects and foetal deaths will be faxed to the DSMB statistician. All other adverse events will be forwarded. The DSMB (see section on ethics) will decide on whether one arm, or the whole study, needs to be terminated. Suggested guidelines for this following the first meeting of the DSMB is that the DSMB would take note following one SAE in an arm, and consider whether an arm needed to be terminated after 2, but would review in the light of data at that stage. The DSMB wishes to be informed if there is a fall in haemoglobin of  $>4$  g/dl, OR where haemoglobin falls below 5 g/dl and these will be treated as a potential SAE, but since most such drops will be secondary to the natural history of the disease these will be noted and discussed, but treated differently from other SAEs.

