*Drug resistance:* Increasing chloroquine resistance has necessitated changing the first line antimalarial drug to sulfadoxine/pyrimethamine (SP) in many countries in Africa. Emerging resistance to SP is increasing at an alarming rate. Drug sensitivity tests conducted recently by the East Africa Network for Monitoring Antimalarial Treatment (EANMAT) have shown SP-treatment failure rates of  $\geq 25\%$  at several sites (EANMAT, 2001a), the threshold level of drug resistance recommended by the WHO for changing an antimalarial drug. Nonetheless, options of alternative drugs are limited because the few available drugs are either not recommended for use as monotherapy (artemisinins), are expensive (mefloquine, Malarone), have inappropriate dosage schedule for outpatient use (quinine), or have an uncertain safety profile in pregnancy.

*Drug resistance within the study area:* The study will be done in Muheza district, where there is already considerably expertise in running clinical trials successfully under the direction of [name], currently seconded to the Gates malaria programme from NIMR. Muheza district participated in the study on “Malaria chemosuppression during pregnancy” by [name] *et al.* (1993) and the LSHTM has long-standing research links in this area. The lowlands of Muheza district experience hyperendemic to holoendemic malaria (Clyde 1967; MARAMAP 2000). More than 95% of the malaria infections are caused by *Plasmodium falciparum*. Resistance of *P. falciparum* to SP is relatively high in the district, providing a strong rationale for using this site to test new combinations that might be adopted nationally. In a recent study in Muheza, the 14-day parasite clearance by SP was 55% ([name] *et al* 2001). In this study, re-treating malaria clinical episodes emanating from parasitaemia that failed first treatment with SP resulted in higher SP-resistance (61%). In contrast, a 3-day course of chlorproguanil-dapsone (LapDap) cleared all but 7% of the parasitaemia. EANMAT data from Mkuzi Health Centre

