## **6.3 Clinical treatment and investigations.**

All women enrolled will be admitted to the research ward (to be built by the GMP) for the first three days for DOT and to monitor clinical response and adverse events. Drugs will be administered by nurses employed by the project. After each administration, the patient will be observed for 45-60 minutes to ascertain drug retention. The dose will be repeated if vomiting occurs within the observation period, and any further vomiting will cause withdrawal from the study and treatment with parenteral quinine. Patients will be treated for symptoms by standard treatment e.g. paracetamol for fever. Women will also continue to receive routine antenatal medicaments of iron supplements, folic acid, and Tetanus Toxoid (TT) given by the MCH. Drugs with an antimalarial activity will not be permitted; if these are essential, the subject will be withdrawn.

Vital signs (temperature, pulse) will be monitored eight hourly during the treatment period and once daily during the remaining period of hospitalisation. Blood pressure will be measured once daily during hospitalisation. Patients will be interviewed using a “clinical assessment form” check list which includes: weakness, chills/rigors, headache, myalgia, dizziness, abdominal pain, anorexia, nausea, vomiting, diarrhoea, palpitations, insomnia, pruritus, coughing, and tinnitus. Blood glucose will be measured on admission and regularly through treatment by glucose stix testing.

Foetal viability (presence of foetal heartbeat) will be monitored daily during admission using a Doppler machine, and at each follow-up visit.

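### Section 9 relies on a three-day admission to make escape medication timely for failures that can run to day 28, and its 40% check at the 50th enrolment does not say how women still in follow-up count

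*Protocol*

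**What the plan says.** Section 9 sets the expectation for the control arm: "We assume that around 45% of women in the SP group will need escape medication". It then gives the safeguard: "Since all women will be admitted to the study ward, the escape medication will be administered on time", and concludes that complications should be minimal. No other safeguard is named there.

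Section 6.3 gives the length of stay: "All women enrolled will be admitted to the research ward (to be built by the GMP) for the first three days for DOT". Appendix 2 repeats it. Contact after discharge is in section 6.6: "Village Health Workers will visit them daily at home up between discharge and day 7, and if they do not attend follow up". There are also clinics on days 7, 14, 21 and 28, open attendance for any complaint, and home tracing of women who miss a clinic.

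The 45% can be traced to the Background (section 2): "In a recent study in Muheza, the 14-day parasite clearance by SP was 55" per cent. The sample size section reuses it as a floor over a longer window: "the proportion of women with treatment failure by day 28 in the SP+Placebo group will be at least 45" per cent. Section 4.1 defines treatment failure by day 28 through six criteria.

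For the efficacy check, section 9 says that if 40% or more of the women in any arm need escape medication, "we will discontinue that arm when 50 women are enrolled". It attaches confidence limits of 25-55% to the estimated treatment failure rate.

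**The concern.** There are two linked problems.

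First, the reason given for tolerating a high expected failure rate does not match the length of stay. Presence on the ward for three days cannot by itself make escape medication timely for a rate measured at 14 days and carried forward to day 28. Section 9 is headed as finalised after the DSMB met, so an incomplete rationale stands in the text that the board's discussion led to.

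Second, the only numerical efficacy stopping rule is triggered by enrolment, while the event it concerns accrues over 28 days. When the 50th woman enters an arm, the latest entrants have had only part of their follow-up. The text does not say whether they are left out, awaited, or counted as not having failed. If they are counted as not having failed, the error has one direction: the observed proportion is too low, and an arm above the threshold may be allowed to go on recruiting.

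**Working it through.** **Rationale against length of stay**

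- Origin of the 45%: 1 − 0.55 = 0.45, a day-14 clearance-failure figure.
- Admission: the first three days (6.3, Appendix 2). Treatment days are numbered 0, 1 and 2 in Appendix 1.
- Section 4.1 criteria: item 1 is limited to the admission, and items 2 and 3 are scored on day 3, at the edge of the stay. Items 4 (day 7) and 6 (day 28) can only be scored after discharge, and item 5 (rescue for recurrence before day 28) arises mainly then.

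The stay therefore covers at most part of the window in which the 45% accrues. Section 6.6 covers the rest to a degree, but section 9 does not rely on it.

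**The plan's own interval**

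For 20/50 = 0.40, the standard error is √(0.40 × 0.60 / 50) = 0.0693. The 95% limits with continuity correction are 0.40 ± (1.96 × 0.0693 + 0.5/50), or 25.4% to 54.6%. This reproduces the stated 25-55%, so that interval takes all 50 women as evaluable.

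**Women still pending at the 50th enrolment in the SP arm**

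- Accrual: 900 women in 450 working days = 2 per working day (sample size section, original plan).
- SP share: 1 in 10 (section 6.2), so 2 × 0.1 = 0.2 SP women per working day.
- Window: 28 days, taken as 20 working days (assumption).
- Pending: 0.2 × 20 = 4 women. If enrolment ran every day, 0.2 × 28 = 5.6.
- Expected failures among 50 at 45%: 22.5. Unseen if none of the pending failures has shown: 0.45 × 4 = 1.8. Unseen if half have shown: 0.9.

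**Chance of reaching 20 of 50 at a true 45%**

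With k pending women kept in the denominator, the count of observed failures is Binomial(50 − k, 0.45) plus Binomial(k, 0.225) if half of the pending failures are seen, or Binomial(50 − k, 0.45) alone if none are seen.

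| Situation | k | Half seen | None seen |
|---|---|---|---|
| Complete follow-up | 0 | 0.80 | 0.80 |
| SP, half the original accrual (assumption) | 2 | 0.77 | 0.73 |
| SP, original allocation and accrual | 4 | 0.73 | 0.64 |
| Equal arms at 2 per day (assumption): 2 × 1/4 × 20 | 10 | 0.58 | 0.32 |

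If the pending women are instead left out and the 40% is applied to the 46 evaluable women, at least 19 failures are needed (0.40 × 46 = 18.4) and the chance is 0.74.

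**The case against.** The strongest reply is that the protocol does look after women once they go home. Section 6.6 gives daily home visits to day 7, smears from febrile women, four clinics and tracing of non-attenders, and section 5.4 provides rescue treatment for failures. This stands. A reader might infer that most failures occur without cover, but no document gives the timing of failures and none shows a gap in care. The defect is in the reason that section 9 states. It also says only that complications should be minimal, which is less than calling the arm safe.

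On the check, a reader might infer that it comes before many of the failures. The protocol's own numbers do not support that for SP: about 2 of 22.5 expected failures would be unseen at most at 4 pending, and fewer with the slow recruitment reported in October 2004. The row with 10 pending combines the original accrual with equal arms, which is only a reading of the revised 72 per arm. It illustrates a faster-filling arm and is not a forecast. Nor should 45% be carried to the other arms as an expectation, since the sample size section projects much lower failure for the two amodiaquine combinations.

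It is also fair to say that the text does not state that pending women count as non-failures. The denominator is left open, not fixed wrongly. Finally, the check is not the only view of efficacy: under Ethical Issues, item 4, the DSMB receives reports of treatment failures. This softens the consequence but does not settle what the 40% is a proportion of.

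**Conclusion.** The point holds in two parts. Section 9's reliance on admission disagrees with the three-day stay in 6.3 and Appendix 2, given a 45% figure measured at day 14 and used to day 28. This follows from the text and needs no assumption. Separately, the 40% check is keyed to the 50th enrolment with no stated follow-up requirement or handling of pending women.

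The size of the second part is moderate for SP. With about 4 women pending, the chance of meeting the criterion at a true 45% falls from 0.80 to 0.73 or 0.64. This rests on pending women staying in the denominator, on 20 working days in 28, on the original accrual and 1-in-10 allocation, and on none or half of the pending failures having been seen. Neither the actual accrual nor the allocation after the October 2004 revision is given, so the effect could be smaller or larger. Correction is worthwhile because this rule bears on pregnant women given a drug that the plan expects to fail often, and the remedy is cheap.

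**What to change.** 1. Reword the section 9 rationale so that it agrees with the three-day admission in 6.3 and Appendix 2 and with the later contact in 6.6, and give the DSMB the corrected statement.

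2. Define the check on a fixed cohort: the first 50 women enrolled in an arm, with escape medication counted to day 28. The existing 40% criterion is met as soon as 20 of those 50 have needed escape medication. Otherwise it is assessed when the 50th woman reaches day 28. A fixed cohort is preferable to counting women who have either completed day 28 or already failed, because that rule admits recent failures while leaving out equally recent non-failures, and so overstates the rate.

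The cost is a change of wording and a note to the DSMB. A negative result becomes final up to four weeks later, with some further enrolment meanwhile: about 0.2 × 20 = 4 SP women at the original rate, or 0.5 × 20 = 10 per arm under equal arms at 2 per day. The DSMB already receives treatment failures during that time. The threshold itself and care after discharge are for the sponsor and the DSMB to reconcile.
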